### Outcome measures

#### Primary outcome measure

The primary outcome measure will be symptom severity, which will be measured with the Dutch version of the Strengths and Difficulties Questionnaire (SDQ
[53,54]). The SDQ will be filled out by parents when the child is between 4 and 11 years old and by children or adolescents when they are between 12 and 17 years old. For the first assessment, the extended versions of the SDQ for both parents and children and adolescents will be used. Each version consists of 25 items on strengths and difficulties and an additional impact supplement. The 25 items are scored on a 3-point scale ranging from 0 (not true) to 2 (completely true). These items are divided into five subscales: emotional symptoms, conduct problems, hyperactivity-inattention, peer relationship problems and prosocial behaviour. A total difficulties score can also be calculated by summing the scores on the emotional symptoms, conduct problems, hyperactivity-inattention, and peer problems subscales (total score can range from 0 to 40). The impact supplement asks whether the respondent thinks the child or adolescents has a problem, and, if so, inquires further about chronicity, distress, social impairment, and burden to others. For the measurements during treatment, the follow-up versions of the SDQ for both parents and children and adolescents will be used. These versions include the 25 items on strengths and difficulties, the impact question and two additional follow-up questions (‘Has the intervention reduced problems?’ and ‘Has the intervention helped in other ways, e.g. making the problems more bearable?’). The parent- and self-report versions of the SDQ have shown acceptable internal consistency, test-retest stability, and parent-youth agreement and good concurrent validity in a Dutch community sample
[54,55]. However, reliability seems insufficient for two subscales of the parent version – conduct problems and peer relationship problems
[56]. Therefore, the total difficulties score of the parent- and self-report versions will be used in the analyses.

#### Secondary outcome measures

Secondary outcome measures will be quality of life, satisfaction with treatment, number of sessions, length of treatment and rate of dropout. Quality of life will be measured with the KIDSCREEN
[57]. The KIDSCREEN-27 parent version will be used for parents of children between 4 and 11 years old and the KIDSCREEN-52 child-adolescent version will be used for children and adolescents between 12 and 17 years old. The items of the KIDSCREEN-27 and the KIDSCREEN-52 are scored on 5-point scales ranging from not at all/never to totally/always. The KIDSCREEN-27 consists of 27 items that can be divided into five subscales: psychical well-being, psychological well-being, autonomy and parent relation, social support and peers, and school environment. The KIDSCREEN-52 consists of 52 items that can be divided into ten subscales: physical well-being, psychological well-being, moods and emotions, self-perception, autonomy, parent relation and home life, financial resources, social support and peers, school environment, and social acceptance (vs. bullying). The KIDSCREEN-27 parent version has shown satisfactory item internal consistency, item discriminant validity and agreement between youth and proxy reports, and good reliability
[57]. The KIDSCREEN-52 child-adolescent version has shown acceptable to satisfactory levels of reliability and validity
[57,58].

Satisfaction with treatment will be measured with the Jeugdthermometer
[59,60]. The parent versions that pertain to the treatment of the child and to the parenting skills training will be used for parents of children and adolescents between 4 and 11 years old. The child version will be used for children and adolescents between 12 and 17 years old. The three respective versions of the Jeugdthermometer consist of 31, 32 and 28 items that are either answered yes/no, ask for a rating or are open-ended. All versions ask for appraisal of information, appraisal of participation, appraisal of the clinician (the child’s clinician or the own clinician), appraisal of the treatment result and for background information. The child version of the Jeugdthermometer has shown acceptable to satisfactory reliability and the parent versions have shown good reliability
[59]. The internal consistency of the parent version that pertains to the treatment of the child has not yet been clearly demonstrated, but the internal consistency of the parent version pertaining to the parenting skills training is good
[59].

The number of treatment sessions will be counted (quantitative variable) and the length of treatment will be registered in days (quantitative variable) for each client. Dropout rates will be calculated as the percentage of clients that abandon treatment (registered as unilateral decision to end treatment) in each feedback group.

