The primary outcome measure will be symptom severity and secondary outcome measures will be quality of life, satisfaction with treatment, number of sessions, length of treatment and rate of dropout. Compared to the first condition, we expect that in the second and third feedback conditions (a) children’s and adolescents’ symptoms will decrease more rapidly and to a greater extent, (b) children’s and adolescents’ quality of life will improve more, (c) children, adolescents and parents will be more satisfied at the end of treatment, (d) treatments will contain fewer sessions, (e) treatments will be shorter, and (f) children, adolescents and parents will drop out of treatment less often. Overall, we expect that the largest effects of feedback will occur in the third feedback condition, where the basic feedback will be enhanced with additional information and practical suggestions, and clinicians will discuss the feedback in case consultation with a colleague. Additionally, we expect that feedback will be most effective for children, adolescents and parents who are not progressing well in treatment (i.e. are NOT).

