### Statistical analyses

All analyses will be conducted using Mplus
[64], because this program allows analyses of complex data while taking into account the longitudinal character of the data. Intervention effects will be analyzed according to the intention-to-treat principle and the completers-only framework. For the intention-to-treat analysis, missing data will be handled using multiple imputations (MI). Descriptive statistics will be calculated for all variables of interest (e.g. symptoms, quality of life, satisfaction with treatment, number of sessions, length of treatment, dropout rate). In order to assess whether randomization resulted in equal groups, we will examine whether there are differences among the three feedback groups on relevant covariates (e.g. sex, age, educational level, ethnicity, socioeconomic status, marital status, household composition and diagnosis) using ANOVA for the continuous variables and Chi-Square tests for the categorical variables. Variables that are distributed differently among the three groups will be entered as control variables in all models testing the effects of the feedback conditions. The hypotheses will be tested using multivariate linear regression analyses. In addition, we will examine whether being NOT moderates the association between the feedback intervention and symptom severity. Therefore, interaction terms will be calculated as the product of the feedback condition and whether or not the client is NOT. These terms will be added as a second step in the multivariate analyses. Reporting of the results of the study will be in accordance with the CONSORT statement
[65,66].

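### Quality of life is measured with a different KIDSCREEN version and informant in each age group, but no common score is named and the stated covariate rule would normally leave age group out

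*Protocol article*

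**What the plan says.** Under Secondary outcome measures, the younger group is assessed by parent report ("The KIDSCREEN-27 parent version will be used for parents of children between 4 and 11 years old") and the older group by self-report ("the KIDSCREEN-52 child-adolescent version will be used for children and adolescents between 12 and 17 years old"). On structure: "The KIDSCREEN-27 consists of 27 items that can be divided into five subscales", whereas "The KIDSCREEN-52 consists of 52 items that can be divided into ten subscales". Items of both forms are "scored on 5-point scales ranging from not at all/never to totally/always".

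Under Aims and hypotheses there is one quality-of-life hypothesis, covering children and adolescents together: "quality of life will improve more" in conditions 2 and 3 than in condition 1. The Participants section adds that the results are meant to generalize to all age groups.

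Under Statistical analyses, "The hypotheses will be tested using multivariate linear regression analyses". The one covariate rule given there is that "Variables that are distributed differently among the three groups will be entered as control variables in all models" testing the feedback conditions. Randomization is stratified by age band (4 to 11, 12 to 17) and by department.

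For the primary outcome, the article does fix an analysis score: the SDQ total difficulties score, range 0 to 40, for both the parent and self-report versions. It gives no equivalent statement for the KIDSCREEN.

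**The concern.** Version, length, subscale structure and informant all change together at age 12. A single all-ages analysis therefore needs two things: a score that means the same in both groups, and a model term that separates the groups. The article names neither for quality of life.

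The covariate rule makes the second gap more than an omission. It adds a variable when the conditions are found to differ on it. Stratification makes age group nearly equal across conditions, so the variable that carries instrument and informant is the one least likely to be added. A stratification factor that strongly predicts the outcome should be in the model because it predicts the outcome, not because it is unbalanced.

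At stake is how precisely quality of life is tested and what its effect estimate means. The choice among raw total, subscales, norm-based scores and separate age groups also has a large effect on power, and left open it could be made after the results are seen.

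**Working it through.** **1. The plan's own figure.** Inputs from Sample size calculation: f = 0.15, alpha 0.05, three conditions, three covariates, N = 432. For the ANCOVA F test, numerator df = 2, denominator df = 432 − 3 − 3 = 426, and noncentrality = f² × N = 0.0225 × 432 = 9.72. Power is 0.801, and 432 is the smallest N that reaches 0.80. The figure reproduces. It is for symptom severity; the article states no power for quality of life.

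**2. Raw scales.** With unit steps on a 5-point item (assumed coding), the sum spans 27 × 4 = 108 points on one form and 52 × 4 = 208 on the other, a ratio of 1.93.

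**3. What the forms share.** Four subscales are named in both lists: physical well-being (printed as *psychical* in the 27-item list, apparently a misprint), psychological well-being, social support and peers, and school environment. The fifth KIDSCREEN-27 subscale, autonomy and parent relation, overlaps two KIDSCREEN-52 subscales. The other four KIDSCREEN-52 domains (moods and emotions, self-perception, financial resources, social acceptance) have no counterpart by name.

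**4. Illustration: raw sums combined with no age or baseline term.** None of these inputs is in the article. Assume items coded 1 to 5, item mean m = 3.3 to 3.7, between-person SD of the item mean s = 0.5 to 0.6, and share aged 4 to 11 p = 0.40 to 0.57.

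Variance ratio = 1 + p(1 − p)(52m − 27m)² / [p(27s)² + (1 − p)(52s)²]

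- Lowest (m = 3.3, s = 0.6, p = 0.40): between = 0.24 × 82.5² = 1633.5; within = 0.40 × 16.2² + 0.60 × 31.2² = 689.0; ratio = 1 + 2.37 = 3.37. Then f = 0.15/√3.37 = 0.082, and power at 432 is 0.31.
- Highest (m = 3.7, s = 0.5, p = 0.57): between = 0.2451 × 92.5² = 2097.1; within = 0.57 × 13.5² + 0.43 × 26² = 394.6; ratio = 1 + 5.32 = 6.32. Then f = 0.15/√6.32 = 0.060, and power is 0.18.

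**5. The same raw sums with the level difference removed.** This is what an age term does, and a baseline score does most of it. With p = 0.5 and the same standardised effect in both age groups, the effect is multiplied by [(27 + 52)/2] / √[(27² + 52²)/2] = 39.5/41.4 = 0.953. So f = 0.143 and power is about 0.76. Most of the loss is recovered. The older group still has (52/27)² = 3.7 times the variance, and the same standardised effect is 52/27 = 1.93 times as many raw points there, so the pooled coefficient is not one interpretable quality-of-life effect.

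**6. Separate analyses by age group.** The age split is not given. At f = 0.15:

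| N in age group (assumed) | Power | f detectable at 80% power |
|---|---|---|
| 144 | 0.34 | 0.26 |
| 216 | 0.49 | 0.21 |
| 288 | 0.61 | 0.18 |

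**The case against.** The strongest reply is that the article never says raw scores will be pooled. It says neither pool nor split. Norm-based scores, item means, or subscales as joint outcomes in a multivariate regression would all fit its wording, and the scoring of a secondary questionnaire is detail that an article commonly leaves to the full protocol or analysis plan, which are not shown. This stands: the missing score would not be a finding by itself, and step 4 illustrates one possible reading, not the plan.

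A reader might infer that the two groups have no common outcome. The documents do not support that. Four subscales are shared by name, and the Intervention section shows that scores from the standard questionnaires are already reported against norms.

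A reader might also infer that age group and baseline are excluded from the models. The article does not say that only unbalanced variables are entered. The sample size section counts three covariates without naming them, the hypothesis concerns improvement, and the analysis is said to respect the longitudinal character of the data. A baseline score may well be intended. Still, the only rule written down for choosing covariates is driven by imbalance, and it points away from the stratification factor.

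Finally, stratification on the same age bands balances version and informant across conditions. This also stands: the randomized comparison is not biased.

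**Conclusion.** The concern holds in a limited form. Instrument and informant are fully determined by age group, the hypothesis covers all ages, no common quality-of-life score is named, and the one stated covariate rule would normally omit age group. The consequence is for precision and interpretability of a secondary outcome, not for the validity of the comparison between conditions.

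Possible power at f = 0.15 runs from about 18% to 31% (raw sums, no age or baseline term), through about 49% (separate groups of 216), to about 76% (raw sums with the level difference removed), against 80% for a common metric with the groups kept together. The first range depends on assumed item means, SDs and age shares; the others depend on assumed age shares and on the primary outcome's effect size being carried over to quality of life. Because no quality-of-life power is claimed, no stated figure is wrong, and the sample size of 432 is unaffected.

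**What to change.** In Statistical analyses, state for quality of life that:

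- age group (the stratification factor), baseline score and baseline-by-age-group are in the model regardless of observed imbalance;
- the all-ages outcomes are the four subscales named in both versions, each standardised to the norms of its own version and informant;
- the domains found only in the KIDSCREEN-52 are reported separately for ages 12 to 17.

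This needs no new data and no change to the questionnaires; the feedback reports already place scores against norms. The cost is that the KIDSCREEN-52-only domains leave the all-ages test. Shared subscale names and norm-based scores put the groups on a common metric, but they do not make parent report and self-report the same measurement, so the age-group term is needed even after standardisation.

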#### Moderator and potential covariates

In addition, we will examine whether being NOT moderates the association between the feedback intervention and symptom severity. We will determine whether each client is NOT by calculating the reliable change index (RCI
[61]) for the total difficulties score on the SDQ. We will calculate the RCI by comparing the total difficulties score at the first measurement during treatment (one and a half months after treatment has begun) with the total difficulties score at the beginning of treatment (baseline assessment). Clients will be designated NOT if the RCI is smaller than 1.96 (i.e. not showing statistically significant improvement).

Lastly, socio-demographic characteristics of the children, adolescents and parents (e.g. sex, age, educational level, ethnicity, socioeconomic status, marital status and household composition) and clients’ diagnosis will be extracted from the electronic patient files and by asking additional questions.

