### Aims and hypotheses

ROM has become an increasingly popular method for improving treatment and has been adopted by many mental health care institutions worldwide
[22,41,42]. Although it seems that feedback from ROM has potential to enhance outcomes in clinical practice, there are still many unanswered questions. There is a need to operationalize and directly compare different approaches to improve the design and delivery of feedback. Also, in order to explain why feedback leads to improvement in some cases but not in others, more insight is needed into the processes underlying feedback. Moreover, barely research has been conducted in real-world clinical practice and outside the United States. Studies that have specifically investigated the effects of feedback in youth mental health care are rare.

The aim of this study is to investigate several potentially effective components of feedback from ROM in youth mental health care in the Netherlands. We will compare three different feedback conditions. In all three conditions feedback will be given to clinicians, will consist of written and graphic performance results, will be compared to norms, will be given at the start of treatment, one and a half months after the start of treatment and every three months during treatment and will be delivered one day after data collection.

In the first feedback condition, clinicians will receive basic feedback regarding clients’ symptoms and quality of life. However, reduction of symptoms or enhancement of quality of life is not always the primary or the single goal of treatment
[43]. Also, children’s and adolescents’ symptoms and problems often arise in interaction with family members
[44]. Furthermore, many children and adolescents have chronic health problems (e.g. ADHD or ASD), which might well persist into adulthood

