### Randomization

Randomization of each participant to one of the three feedback conditions will be carried out using a computer-generated random number list with a blocked randomization scheme (block size 6, randomization ratio [1:1:1]). An independent researcher will allocate the participants to the feedback conditions after the baseline assessment. To ensure that the distribution of parents and children and adolescents is similar across the three feedback conditions, randomization will be stratified by age of the child or adolescent (4 to 11 years old and 12 to 17 years old). To exclude confounding due to differences among departments, randomization will also be stratified by department (Arnhem, Ede, Nijmegen and Tiel).

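### The not-on-track moderator is scored after randomisation on the primary outcome scale, so if the arms already differ at 1.5 months the planned interaction does not estimate effect modification

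*Protocol article*

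**What the plan says.** Under Moderator and potential covariates, NOT status is a reliable change index: "We will calculate the RCI by comparing the total difficulties score at the first measurement during treatment" (1.5 months after treatment begins) with the baseline score. A client is NOT when the index is below 1.96.

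Four other statements bear on this:

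- **Same scale as the primary outcome.** Primary outcome measure, on the SDQ: "Therefore, the total difficulties score of the parent- and self-report versions will be used in the analyses".
- **Allocation comes first.** Randomization: "An independent researcher will allocate the participants to the feedback conditions after the baseline assessment".
- **Feedback precedes the moderator.** Aims and hypotheses, of feedback in all three conditions: it "will be given at the start of treatment, one and a half months after the start of treatment and every three months during treatment".
- **Condition is expected to act early.** In the same section, the hypothesis for conditions 2 and 3 against condition 1 is that "symptoms will decrease more rapidly and to a greater extent".

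Under Statistical analyses, "interaction terms will be calculated as the product of the feedback condition and whether or not the client is NOT", and these terms are added as a second step in the regression. Aims and hypotheses and the Discussion both state the expectation that feedback works best in NOT clients. Strengths and limitations presents the test as a way to learn why feedback works in some cases and not in others. The limitations do not mention that the moderator is measured after randomisation.

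**The concern.** A moderator supports a randomised comparison within its levels only if treatment cannot influence it. Here it can. If the enhanced conditions speed improvement, some clients who would have been NOT under condition 1 become non-NOT under condition 3. Clients who are still NOT under condition 3 are then, on average, those who would have done worse without the extra benefit. The non-NOT group under condition 3 is diluted by clients who crossed the cut-off because of the benefit. In both strata, condition 3 carries the poorer underlying prognosis.

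At stake is one of the trial's stated hypotheses. An apparent extra benefit in NOT clients could arise when every client benefits equally, and the artefact points the way the protocol expects.

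**Working it through.** **1. The plan's own figure.** The protocol gives no calculation for the NOT interaction, only a sample size for the condition effect. With f = 0.15, alpha 0.05, 3 conditions, 3 covariates and N = 432: noncentrality = 0.15² × 432 = 9.72, degrees of freedom 2 and 432 - 3 - 3 = 426, power 0.8007. The figure reproduces and is not in question.

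**2. Effect size used below.** For three equally spaced means -d, 0, d (in SD units), f = d × √(2/3). So d = 0.15 / 0.8165 = 0.184, and condition 3 against condition 1 is 2d = 0.367 SD.

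**3. Assumptions that are not in the document.** SDQ standardised to SD 1; reliability 0.7 to 0.8; correlations between time points 0.5 to 0.75; mean improvement 0.2 SD at 1.5 months and 0.4 SD at the end; a constant additive benefit, so true moderation is zero.

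**4. How condition shifts NOT status (reliability 0.8, baseline to 1.5-month correlation 0.6).**
- Improvement needed to escape NOT: 1.96 × √(2 × (1 - 0.8)) = 1.24 SD.
- SD of change: √(2 × (1 - 0.6)) = 0.894.
- Condition 1: P(NOT) = Φ((1.24 - 0.2) / 0.894) = 0.877.
- Condition 3, with all 0.367 SD present by 1.5 months: Φ((1.24 - 0.567) / 0.894) = 0.774.

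The non-NOT share rises from about 12.3% to 22.6%. Among non-NOT clients in condition 3, (22.6 - 12.3) / 22.6, about 46%, would have been NOT under condition 1. Among NOT clients in condition 1, (22.6 - 12.3) / 87.7, about 12%, would have left that group under condition 3. The distortion is therefore greater in the smaller, non-NOT stratum, and this creates the interaction.

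**5. Simulated condition 3 effect by stratum.** Same setting, three arms, final SDQ regressed on baseline SDQ, condition (linear trend), NOT and their product. Negative means benefit. The last column is the rejection rate of the interaction test at 5%.

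| Early effect (SD) | Final effect (SD) | In non-NOT | In NOT | Interaction | Rejection, N = 432 / 864 |
|---|---|---|---|---|---|
| 0 | 0.367 | -0.370 | -0.369 | 0.001 | 0.028 / 0.030 |
| 0.18 | 0.367 | -0.281 | -0.329 | -0.048 | 0.036 / 0.042 |
| 0.367 | 0.367 | -0.183 | -0.278 | -0.096 | 0.055 / 0.067 |
| 0.6 | 0.6 | -0.310 | -0.443 | -0.133 | 0.078 / 0.106 |
| 0.367 | 0 | +0.179 | +0.087 | -0.091 | 0.046 / 0.068 |

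In the last row the early gain fades completely, and both strata show apparent harm although the true final effect is zero.

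**6. Smaller early effects.** With the true benefit fixed at 0.367 SD, over the assumed range of reliability and correlations, the false interaction is:

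- early effect 0.1 SD: -0.02 to -0.06 SD;
- early effect 0.2 SD: -0.03 to -0.09 SD;
- early effect 0.3 SD: -0.05 to -0.13 SD.

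**7. Form of the outcome.** The statistical section does not fix how baseline enters the model. At an early and final effect of 0.367 SD, the false interaction is -0.057 SD for the unadjusted final score, -0.119 for change from baseline, and -0.113 if the outcome averages the 1.5-month and final scores.

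**8. Against sampling error.** For two arms of 144 with early effects of 0.1 to 0.3 SD, the standard error of the interaction is about 0.28 to 0.38 SD. It is wide because few clients are non-NOT: in condition 1 of step 4, 144 × 0.123, or about 18. Rejection there was 3.7% to 4.8%, against 3.3% to 4.3% with no early effect.

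**The case against.** The case on the other side has five parts.

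- **The bias is conditional.** With no arm difference at 1.5 months the interaction is unbiased (first row of the table), and the protocol states no 1.5-month effect. This stands. A reader might infer that the planned interaction is biased whatever happens; the document does not support that.
- **When the arms first diverge is not fully clear.** The start-of-treatment feedback is described as common to all conditions. What sets conditions 2 and 3 apart relies on a questionnaire completed only in those arms, yet allocation follows the baseline assessment. On one reading the arms separate only at the 1.5-month measurement, and the bias would then be close to zero. The timing sentence equally allows condition-specific feedback from the start, and the hypothesis of a more rapid decrease points that way. The point stays open, which is why the size is given as a range.
- **The bias is small against sampling error.** This stands. A reader might infer serious inflation of the type I error. At N = 432 the rejection rate stays at about 3% to 6% for effects up to 0.367 SD. It rises clearly only with larger early effects or a larger sample.
- **It is an additional analysis.** The first-step condition effects are untouched, which limits the severity. But the moderation is a stated hypothesis and is presented as a strength of the design.
- **A baseline-defined moderator asks a different question.** The hypothesis concerns clients who are not progressing in treatment, not those predicted at baseline to respond poorly. This stands. A reader might conclude that the NOT definition must be replaced by a predicted-risk score, but that would answer another question and need a new model fitted in about 144 control clients.

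NOT is also unknown for the roughly 50% expected to stop after baseline. That is a separate missing-data matter, partly met by inviting twice as many families and by multiple imputation.

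**Conclusion.** The concern holds in conditional form. NOT is measured after randomisation, after feedback has begun, and on the primary outcome scale. If condition changes early symptoms, as the protocol predicts, the condition by NOT product does not estimate effect modification and the stratum effects are not randomised comparisons.

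For assumed early effects of 0.1 to 0.3 SD and a constant true benefit of 0.37 SD, the false interaction is roughly -0.02 to -0.13 SD, towards the hypothesised larger effect in NOT clients, and both stratum effects are attenuated. These figures rest on the assumed reliability, correlations and mean improvement, and fall to about zero without an early arm difference. At the planned size the false-positive rate stays near 5%. The damage is to the meaning of the estimate and of the subgroup effects, not to the error rate or the main condition comparison.

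**What to change.** - **Moderator and potential covariates; Statistical analyses.** Label the 1.5-month NOT analysis exploratory. Report NOT proportions by condition first, since a difference between arms shows directly that condition affects the moderator. Then run a landmark analysis of outcomes after 1.5 months, among clients with a 1.5-month score.
- **Strengths and limitations.** Draw no causal moderation claim from this analysis. Amend the text that presents it as showing why feedback works in some cases, and name the post-randomisation measurement as a limitation.
- **A moderation test protected by randomisation.** Add an interaction between condition and a variable fixed before allocation, such as the baseline SDQ total difficulties score. A cross-validated predicted-risk model is optional.

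The cost is wording and one extra model, using data already collected. The downside is that the hypothesis about observed early non-response is answered only descriptively, and the baseline interaction addresses a related but different question.
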